## Abstract

**Background:**

Family members, who provide the majority of care for persons with dementia, are especially vulnerable to developing depression. Interventions targeting their depressive symptoms have been proposed but their efficacies vary considerably. It has been suggested that interventions carried out in the home setting and involving both caregivers and care recipients are more efficacious. This study aims to compare the efficacy of a home-based structured exercise programme involving both persons with dementia and their caregivers with nonexercise social contact control in treating depression among caregivers.

**Methods/design:**

This is a parallel-group, assessor-blind, randomised controlled trial. A total of 136 caregiver-care-recipient dyads (i.e. 272 participants in total) will be recruited and randomly allocated to either a home-based structured exercise (sitting Tai Chi) group or a social contact control group. The trial comprises a 3-month intervention phase followed by an extended observation phase of another 3 months. All participants will be assessed at baseline, 6th week, 12th week and 24th week. The primary outcome will be the reduction in depression among caregivers as measured by the Hamilton Rating Scale for Depression. The secondary outcomes will be burden, quality of life, cognitive performance and balance ability of the caregivers, as well as the neuropsychiatric symptoms, cognitive function, balance and functional abilities of the persons with dementia. We will also examine whether the brain-derived neurotrophic factor gene modulates mood changes in response to exercise.

**Discussion:**

The findings offer a potential avenue of intervention by providing a low-cost, safe and effective treatment for depression among dementia caregivers, which may in turn also benefit the care recipients.

**Trial registration:**

ClinicalTrials.gov Identifier: NCT02132039, registered on 28 April 2014.

## Background

Dementia affects over 47 million people worldwide [1]. It causes decline in cognitive function, impairment in activities of daily living, and is associated with significant behavioural and psychological symptoms among the persons affected. Since the majority of dementia care is provided by family members [2], it is not surprising that they suffer from a high level of psychological distress and burden. It is now evident that informal caregivers of persons with dementia are at an elevated risk of developing depression and anxiety, and report poorer quality of life [3–5]. They also experience more stress than those who care for someone with physical disorders [6]. In a local study interviewing family caregivers of older adults with dementia in Hong Kong, they suffered significant stress and reported various negative emotions, conflicts between social roles, and difficulty in providing daily care and managing the care recipients’ behaviours [7]. Dementia caregiving has, therefore, emerged as a pressing health care issue.

In view of this, different interventions have been developed to alleviate depressive symptoms among caregivers of dementia persons. Recent reviews have analysed the efficacies of educational [8] and social support (e.g. befriending and peer support, family support and social network interventions, and support groups) [9], and psychological [10] and Internet-based interventions [11] for caregivers of persons with dementia. Though clinically meaningful, these interventions achieved only small effects [8, 11] or inconsistent results [9]. This may be partly because the programme goals and target groups were not clearly defined. Therefore, it has been suggested that research should focus on subgroups of caregivers such as depressed caregivers [12].

Among interventions for depression, exercise therapy has drawn much attention from researchers and practitioners. Exercise is a subset of physical activity that is planned, structured, repetitive and purposeful, and regular exercise compares favourably to antidepressants as treatment for milder depression [13]. Though its antidepressant mechanism is not yet clear, evidence suggests that exercise improves mood by normalising brain-derived neurotrophic factor levels [14], modifying serotonin function and releasing endogenous opioids [15]. More recently, exercise is reported to reduce atrial natriuretic peptide and brain natriuretic peptide, and to enhance copepetin and growth hormone among depressed individuals [16]. In addition, exercise improves one’s psychological and social sense of wellbeing [15]. It is, therefore, not surprising that a recent meta-analysis showed that exercise had a large and significant effect on depression (standardised mean deviation adjusted for publication bias = 1.11) with a fail-safe number of 1057 [17].

There has been emerging evidence supporting the effectiveness of exercise in treating depression in dementia caregivers. In a recent study, 17 caregivers participating in regular exercise of moderate intensity experienced less sense of burden and fatigue, and reported better sleep when compared with those in the control group [18]. Encouraging results have also been reported with endurance exercise [19], yoga [20], walking [21], and a combination of various physical activities [22].

However, the number of exercise studies for caregivers remains limited, and the sample sizes involved are usually small. This is probably related to the difficulty for dementia caregivers of participating in centre- or community-based exercise interventions because they are unable to find someone to take care of the care recipients, and lack time for additional activities [23]. In some previous studies, caregivers also voiced a preference for a programme that both caregiver and care recipient can participate in [22]. Home-based programmes involving both caregivers and care recipients may offer a possible solution [24]. Not only does the home-based dyadic intervention improve treatment adherence [25], it is also more successful in enhancing care-recipient function and reducing caregiver sense of burden [26].

We therefore propose to conduct the following assessor-blind randomised controlled trial of a home-based exercise intervention for both dementia caregivers and their care recipients.

### Objectives

The objectives of the study are as follows:To evaluate the effect of a home-based exercise programme on: caregivers’ depressioncaregivers’ burden, quality of life, cognitive performance and balance abilityneuropsychiatric symptoms, cognitive function, and balance and functional abilities among persons with dementiaTo assess whether the brain-derived neurotrophic factor (*BDNF*) gene modulates mood changes in response to exercise intervention

## Methods/design

### Design

This is a parallel-group, assessor-blind, randomised controlled trial, which comprises a 3-month intervention phase followed by an extended observation phase lasting for 3 months. Participants will be randomly assigned to either the home-based structured exercise (intervention) or the standard nonexercise social contact (control) group. The study is registered with ClinicalTrials.gov (NCT02132039), and conducted in accordance with the Declaration of Helsinki. Ethics approval has been sought from respective Institutional Review Boards. All results will be reported according to the Consolidated Standards of Reporting Trials (CONSORT) 2010 Statement [27]. A CONSORT flow diagram of the study is depicted in Fig. 1.

**Fig. 1 Fig1:**
[figure not shown]
Consolidated Standards of Reporting Trials (CONSORT) flow diagram of the home-based exercise trial

### Participants

Caregiver-care-recipient dyads will be recruited from psychogeriatric and geriatric outpatient clinics and various community centres for elders in Hong Kong by convenience sampling. Potential participants will be identified by the research team and screened for eligibility based on the inclusion and exclusion criteria. Informed consent will be obtained from all eligible participants before enrollment.

### Inclusion criteria

Caregivers:Aged 50 years or aboveInformal caregivers, i.e. unpaid family members who offer a substantial amount of care for the persons with dementiaGeriatric Depression Scale (GDS) [28] score >0 but <8 (i.e. the local cut-off score for clinically significant depression)Understand ChineseReceiving antidepressant treatment on a steady dose for at least 3 months (if applicable)

Care recipients:Aged 60 years or aboveDementia diagnosis confirmed by a physicianDependence in at least one of the activities of daily living (ADL)Mini Mental State Examination (MMSE) [29] score >10

### Exclusion criteria

Both caregivers and care recipients:No regular (i.e. at least three times/week) Tai Chi practice or other forms of mind-body exercise such as yoga, *qigong*, or mindfulness training in the past 6 monthsPresence of any condition which renders participants unsuitable for physical training, for example, severe psychotic symptoms, imminently suicidal, significant orthopaedic problems, or unstable medical conditions

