### Intervention

The intervention consists of eight home-based sessions of sitting Tai Chi. Tai Chi is a traditional Chinese exercise that combines rhythmic and flowing patterns of bodily movements with coordinated breathing and mindful meditation [30]. It is a moderate-intensity aerobic exercise at about 3 to 6 metabolic equivalents [31]. It has been successfully implemented in the local older population [32] and, as a low impact exercise, it is associated with a lower risk of musculoskeletal injury making it a suitable form of exercise for older adults. Since the current study includes persons with significant cognitive impairment, we adopt sitting Tai Chi which is a simpler version of Tai Chi developed by Hong Kong Polytechnic University [33]. The exercise consists of 12 steps, which include weight shifting in different sitting positions, trunk and upper limb movements, and alternate thigh lift in a smooth and coordinated manner [33].

Four weekly exercise sessions will be arranged over the first 4 weeks, and four more biweekly sessions over the next 8 weeks. Each session will last for 1 h, which starts with 10 min of warm-up activities followed by 40 min of sitting Tai Chi practice and, lastly, 10 min of cool-down exercises. The caregiver-care-recipient dyads will practise Tai Chi in their home under the instruction of a Tai Chi teacher with more than 20 years of teaching experience, and a trained research assistant. In order to monitor the progress and address participants’ concerns, biweekly phone contacts will be made during the study period (12 scheduled phone contacts in 24 weeks). On completion of the eight home-based Tai Chi sessions, participants will be given a manual and training video with detailed instructions of the Tai Chi poses to facilitate their continuation of Tai Chi practices.

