A standard nonexercise social contact will be provided to the participants in the control group. Since social contact may be beneficial to one’s mood and may contribute to any improvement observed in the intervention group, we provide participants in the control group with a level of social contact equivalent to the intervention group. They will be visited by the research assistant eight times over 12 weeks. The visits involve a series of conversations related to neutral topics that are designed according to the principles of a befriending programme [34]. These topics are structured and standardised, and do not involve any topic concerning physical activity. Similar to the intervention group, 12 biweekly phone calls will be made during the study period to offer a comparable level of social contact.

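### The prior-practice item in the exclusion list is worded in the negative, so as written it excludes newcomers to Tai Chi and lets regular practitioners through

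*Protocol article*

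**What the plan says.** The Participants section of the protocol article states that candidates are "screened for eligibility based on the inclusion and exclusion criteria". The list headed "Exclusion criteria" applies to both members of the dyad and has two items. The first begins "No regular (i.e. at least three times/week) Tai Chi practice or other forms of mind-body exercise such as yoga" and goes on to name other mind-body practices, with a look-back of six months. The second is the presence of a condition that makes a person unsuitable for physical training.

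The inclusion list has separate entries for caregivers and care recipients. It covers age, caregiving role, depression score, language, antidepressant use, dementia diagnosis, dependence and cognitive score. It does not mention earlier Tai Chi or other mind-body practice.

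On the two arms, the Intervention section says: "The intervention consists of eight home-based sessions of sitting Tai Chi". For the comparator it says: "A standard nonexercise social contact will be provided to the participants in the control group". The Trial status section reports that recruitment was still open when the article was submitted.

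**The concern.** The heading and the item each carry a negation, and together they reverse the rule. Someone who meets an exclusion criterion may not enter. The first item is met by a person who has *not* been practising regularly. Taken at its word, the list keeps out the people a trial of newly taught Tai Chi would want and does not keep out those already doing the same kind of exercise.

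The rule governs prior exposure to the experimental treatment itself. Regular practitioners could enter either arm. In the control arm they would bring mind-body exercise into a condition designed to contain none. In the Tai Chi arm they would have less to gain from being taught. Either way the contrast the trial is meant to test would be weakened. The list would also be carried into the trial report, and anyone replicating the trial would take it over.

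**Working it through.** No arithmetic applies. The question is which way one criterion points, so the relevant sections are set side by side.

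**Step 1: the literal rule.** The inputs are the heading (a person who meets an item is ineligible) and the item (absence of regular practice, meaning at least three times a week, over six months).

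| Person | Meets the item as written? | Result as written | Result with *No* deleted |
|---|---|---|---|
| No regular practice | Yes | Excluded | Not excluded by this item |
| Regular practice | No | Not excluded by this item | Excluded |

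The two result columns are exact opposites.

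**Step 2: is the list a set of requirements under the wrong heading?** If both items were conditions for entry, the negative wording would be harmless. The second item rules this out. It names the presence of an unsuitable condition, which works only as a reason to exclude. The two items therefore point in opposite directions, and no single reading of the heading makes both sensible.

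**Step 3: is the rule stated correctly elsewhere?** The inclusion list is silent on prior practice. The abstract, the Design and Participants sections and the Discussion do not restate the rule either. The exclusion list is the only source, so a reader cannot settle the matter by comparing two versions.

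**Step 4: which direction fits the design?** The Intervention section describes teaching a simplified twelve-step sitting form over eight visits with an instructor, followed by a manual and video so that participants can continue. The control visits are structured conversations that keep away from physical activity. Both fit participants who do not already practise. The literal rule fits neither.

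**Step 5: is the item used?** Yes. The Participants section makes the two lists the basis for screening.

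The item is therefore inverted as written, the intended direction can be inferred from the design, and nothing in the article corrects it.

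**The case against.** The strongest reply is that no competent screener would follow the literal wording. The intended meaning is plain from the description of both arms. The screening was done by the research team, and a journal article condenses a fuller protocol and a screening form that are not shown here. On this view the fault is editorial.

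Most of that stands. The intent is recoverable, and nothing in the article shows that the literal rule, or a mixture of the two readings, was used at screening. What does not stand is that the point can be ignored. The article does not leave this criterion to another document. It states the rule, and states it the wrong way round, in the list it names as the basis for eligibility.

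Two stronger readings are tempting, and the documents support neither.

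- A reader might infer that the enrolled population is wrong or contaminated with regular practitioners. The article gives no screening results and no account of how the item was applied, so this is unknown.
- A reader might infer a definite loss of power, by supposing that some share of enrolled dyads already practise and gain nothing more. The documents give neither that share nor any support for assuming no further gain. A figure built on them would describe the assumptions and not this trial, so none is offered here.

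**Conclusion.** The point holds as an error in a stated eligibility rule. As written, the criterion excludes people without prior practice and does not exclude regular practitioners, for caregivers and care recipients alike. It is very probably a drafting slip.

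Its size is one item in one list. It does not change the endpoint, randomisation, sample size or analysis. Its effect on the trial depends on a fact the article does not give, namely which rule the screening form carried. If screeners applied the evident intent, the harm is limited to the clarity and reproducibility of the eligibility criteria. Only if the literal wording was used, for some or all dyads, would the trial population be affected.

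The conclusion rests on the ordinary meaning of an exclusion list, which the second item confirms. The judgement that it is a slip rests on the descriptions of the two arms.

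**What to change.** Reconcile the heading and the wording in one of two ways: delete *No* so that regular practice becomes the reason for exclusion, or move the sentence unchanged to the inclusion criteria for both members of the dyad.

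Because recruitment was open at submission, also:

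1. Check the wording on the screening form and in the full protocol.
2. Confirm from the screening log which rule was applied, to dyads turned away as well as to those enrolled.
3. Report any dyad enrolled contrary to the corrected rule. If there are none, say so in one sentence.

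The cost is a one-word correction, or the move of one sentence, plus one pass through the screening records. The sample size and the analysis need no change.

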### Randomisation and blinding

Participants will be randomly assigned to either the intervention or the control group using a computer-generated block randomisation sequence (block sizes of 4). Randomisation will be performed by an independent team member who will not be involved in the recruitment, assessment, or delivery of the intervention. The allocation sequence will be concealed from the study investigators and research staff in sequentially numbered, opaque, and sealed envelopes. The assessor for clinical parameters will be blinded to the randomisation status, and the trainer who conducts the intervention will be blinded to the assessment results.

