### Sample size calculation

The sample size is calculated by the proportion of caregivers who respond to the intervention as indicated by the HAM-D-17. Taking reference of the previous study [49], we expect a 30 % reduction in the proportion of participants rated as depressed in the control group with social contact only. Assuming that a further 30 % reduction is achieved by sitting Tai Chi, we need 56 caregiver-care-recipient dyads (i.e. 112 participants) in each arm to identify a significant effect at a two-tailed alpha of 0.05 and 80 % power. Allowing for 20 % dropout, the number of dyads in each arm will rise to 68. A total number of participants of 272 will be recruited.

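### One fixed block size of 4, with delivery staff not separated from recruiters, leaves an avoidable risk that upcoming allocations can be predicted

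*Protocol article*

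**What the plan says.** Under Randomisation and blinding, the protocol article allocates "using a computer-generated block randomisation sequence (block sizes of 4"). It gives one size and mentions no random variation. The same section sets two safeguards: "Randomisation will be performed by an independent team member who will not be involved in the recruitment, assessment, or delivery of the intervention", and "The allocation sequence will be concealed from the study investigators and research staff in sequentially numbered, opaque, and sealed envelopes". The assessor of clinical parameters is blinded to allocation. The trainer is blinded to assessment results, not to arm.

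Under Participants, "Potential participants will be identified by the research team and screened for eligibility". Under Intervention, the Tai Chi sessions take place "under the instruction of a Tai Chi teacher with more than 20 years of teaching experience, and a trained research assistant". For the control group, "They will be visited by the research assistant eight times over 12 weeks".

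The abstract gives the total: "A total of 136 caregiver-care-recipient dyads (i.e. 272 participants in total) will be recruited and randomly allocated". The sample size section gives the split: "the number of dyads in each arm will rise to 68".

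**The concern.** A sealed envelope hides the next assignment. It does not hide assignments already carried out, and here these are visible to anyone who delivers the sessions, because Tai Chi and befriending conversation cannot be mistaken for each other. With one constant block length, past assignments carry information about the next one, and sometimes settle it.

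That matters if the information reaches someone who can influence which dyad is enrolled next, or when. The article keeps the person who randomises apart from recruitment, assessment and delivery. It does not say that those who recruit are kept apart from those who deliver. If the two groups overlap or share information, foreknowledge could lead to selective enrolment, and the arms could then differ at baseline in severity or motivation, which allocation is meant to prevent.

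**Working it through.** The article states no predictability figure, so there is none to reproduce. The inputs are:

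- Block size 4 (Randomisation and blinding).
- Allocation 1:1, since each arm has 68 dyads (Sample size calculation), so each block holds 2 of each arm.
- 136 randomised units, taking the dyad as the unit (Abstract), which gives 136/4 = 34 complete blocks if there is one list.

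**Certain allocations.** An allocation is certain when one arm's two places in the block are already filled. There are 6 possible blocks:

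- AABB and BBAA leave the last 2 allocations certain.
- ABAB, ABBA, BABA and BAAB leave only the last 1 certain.

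Expected number certain per block = (2 × 2 + 4 × 1)/6 = 4/3. As a share of 4 this is 1/3, or 33.3%. Over 34 blocks, 34 × 4/3 = 45.3 dyads. The last allocation of every block is always certain, so the share never falls below 34 of 136 (25%).

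**Best guessing.** The rule is to guess the arm that is behind in the block, and to toss a coin when the arms are level. The chance of being right at each position is:

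- Position 1: 1/2.
- Position 2: 2/3.
- Position 3: certain with probability 1/3, otherwise a coin toss, so 1/3 × 1 + 2/3 × 1/2 = 2/3.
- Position 4: 1.

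The sum is 17/6, and 17/6 divided by 4 is 17/24 = 70.8%, against 50% under simple randomisation.

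**Alternatives.** For a fixed, known block of 2m, the certain share is 1/(m + 1): 1/4 for size 6 and 1/5 for size 8. For randomly varying sizes, an observer was simulated who sees the whole allocation history in order, knows which sizes are possible but not which one is in use, and updates the probabilities exactly (136 units, 1,500 runs, sizes equally likely):

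| Scheme | Certain | Guessed correctly |
|---|---|---|
| Fixed 4, known | 33.3% | 70.8% |
| Fixed 6, known | 25.0% | 68.3% |
| Varying 4 and 6 | about 5.5% | about 69.2% |
| Varying 4, 6 and 8 | about 2.2% | about 67.9% |

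Varying the size removes most of the certainty but little of the guessing advantage.

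**The case against.** The strongest objection is that the figures describe an observer whom the article never places in recruitment. It says that the research team screens and that a research assistant attends sessions. It does not say that the assistant recruits, that the same individual serves both arms, or that allocations are passed to recruiters. Delivery staff see overlapping 12-week visit schedules, which need not reveal envelope order or where a block begins. Staff separation is also a detail that an article may leave to the full protocol. All of this stands, and it is why the one-third figure must be conditional.

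Several stronger readings are tempting but unsupported:

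- A reader might infer that recruiters learn every earlier allocation. No section says so.
- A reader might infer a single unstratified list. The article is silent on stratification and on the number of lists, and it names several recruitment sources.
- A reader might infer that the block size was published while recruitment continued. The Trial status section shows recruitment open at submission only.
- A reader might take convenience sampling to mean that the team controls the order of enrolment. It describes where dyads come from, and screening against the criteria still applies.
- A reader might infer that assessor blinding is compromised. The assessor is stated to be blinded, and the block size by itself opens no route to the assessor.

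What the objection does not remove is the mechanism. An independent randomiser and sealed envelopes protect the content of the next envelope; they do not stop it from being deduced from past allocations. The single block size is a choice the article states, not a detail left out.

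**Conclusion.** The point holds as an avoidable risk of selection bias, not as shown bias. A person who knows the block size, the block boundaries and the earlier allocations in order can predict on average 33.3% of allocations with certainty and guess 70.8% correctly. The count of about 45 of 136 dyads also assumes one list of 34 complete blocks with the dyad as the unit. Bias would follow only if that person could also influence who is enrolled or when. The article neither states nor excludes either condition. This is a cheap improvement to a stated design choice; nothing in the plan is miscalculated or contradictory on this point.

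**What to change.** If recruitment is still open, complete the current block. Then have the independent team member generate the remaining sequence with randomly varying block sizes, for example 4 and 6. Do not disclose the sizes to recruiting, delivering or assessing staff, and keep past allocations from those who screen and enrol. The second measure matters as much as the first, because varying the size leaves best guessing at about 69.2%. The fall in certain allocations to about 5.5% applies only to dyads randomised under the new sequence.

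The cost is a mid-trial change to the randomisation procedure, which must be documented, with a new list and new envelopes. A final block of 6 cut short could leave the arms unequal by up to 3 dyads.

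If enrolment has closed, the list cannot be changed. Report the fixed block size, and who had access to past allocations, as a limitation.
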